### Interventions

Subjects providing written informed consent will be invited for the following visits (Figure 1):

**Figure 1 F1:**
[figure not shown]
**Timetable and characteristics of all visits.** *Patients only, Treatment = intradetrusor onabotulinumtoxinA injection, MRI = magnetic resonance imaging, PVR = post void residual

Screening (Visit 1): Evaluation for study eligibility will be based on medical history, urinalysis to exclude urinary tract infection (UTI) and pregnancy in female participants, 3-day bladder diary, post void residual, urodynamic parameters as well as on standardised validated questionnaires such as Qualiveen [22] and International Consultation on Incontinence modular questionnaire [(ICIQ), Bristol Urological Institute, Southmead Hospital Bristol, UK] assessing lower urinary tract symptoms (LUTS) in both woman (ICIQ-FLUTS) and men (ICIQ-MLUTS).MRI measurements (Visit 2 and 3, Figure 1): Two MRI measurements will be performed in identically manner within a 5 to 7 weeks interval.Both MRI measurements will be performed using a Philips Ingenia 3 Tesla MR scanner (Philips Medical Systems, Best, The Netherlands) with a 16-channel head coil to acquire the following sequences (Figure 2):

**Figure 2 F2:**
[figure not shown]
**Sequences of magnetic resonance imaging (MRI) measurements.** *Bladder will be filled with body warm saline until a persistent desire to void is present.

• Structural sequences will comprise T1-weighted and DTI.• Functional sequences will comprise three different task-related fMRI paradigms (Figure 3).

**Figure 3 F3:**
[figure not shown]
**Scan paradigm of three different task-related functional MRIs (fMRIs).** All task-related fMRIs identically start with a ‘baseline’ rest (60 s, no specific stimulus or task is performed), a ‘baseline’ rating (desire to void and level of pain), a short rest (jittered between 7 and 9 s in which blood oxygen level-dependent (BOLD) activation resulting from motor activity during the previous rating will return to baseline to avoid contamination of the following condition) and conclude with a ‘last’ rest (60 s, no specific stimulus or task is performed). All task-related fMRIs consist of eight repetitive blocks, each with either five (first and third fMRIs) or eight (second fMRI) conditions. **(A)** Conditions of the first task-related fMRIs: (1) automated infusion of 100 mL body warm saline, (2) plateau phase (bladder distention after infusion is perceived), (3) rating, (4) passive withdrawal to empty the bladder completely and (5) short rest. This task-related fMRI starts with an empty bladder. **(B)** Conditions of the second task-related fMRIs: (1) automated infusion of 100 mL warm saline, (2) plateau phase, (3) rating, (4) short rest, (5) automated withdrawal of 100 mL, (6) plateau phase (bladder distention after withdrawal is perceived), (7) rating and (8) short rest. *This task-related fMRI (B) starts with a high prefilled bladder volume, that is, the bladder will be filled with body warm saline until a persistent desire to void is present. **(C)** Conditions of the third task-related fMRIs: (1) automated infusion of 100 mL cold (4–8°C) saline, (2) plateau phase, (3) rating, (4) passive withdrawal to empty the bladder completely and (5) short rest. This task-related fMRI starts with an empty bladder.

• In the first two task-related fMRI paradigms, we will examine the effect of visceral bladder sensation by automated, repetitive bladder filling with 100 mL body warm (37°C) saline starting with an empty bladder (first paradigm) and a bladder volume eliciting desire to void (second paradigm).

• The third task-related fMRI paradigm will contain automated, repetitive filling of 100 mL cold (4-8°C) saline starting with an empty bladder.

Repetitive filling will be performed using an automated MR-compatible and MR-synchronised pump system [18] to precisely fill and drain the bladder. During the MRI measurements, all participants will use an MR-compatible handheld response system [23] to rate their desire to void and level of pain on a displayed visual analogue scale.

### Study outcome measures

#### Primary

(A) Task-related BOLD signal intensity in supraspinal regions of interest (ROI) in SCI patients with neurogenic detrusor overactivity compared to healthy controls.

(B) Supraspinal morphometry of ROIs in SCI patients with neurogenic detrusor overactivity compared to healthy controls.

(C) SC and FC between ROIs of the supraspinal LUT controlling circuitries in SCI patients with neurogenic detrusor overactivity and healthy controls.

(D) Changes of task-related BOLD signal intensity, SC and FC between ROIs in SCI patients with neurogenic detrusor overactivity before and after study independent intradetrusor onabotulinumtoxinA injections.

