**Methods/Design:**

This is a prospective structural and functional magnetic resonance imaging study investigating the supraspinal lower urinary tract control in healthy subjects and spinal cord injury patients undergoing intradetrusor onabotulinumtoxinA injections for treating neurogenic detrusor overactivity.

Neuroimaging data will include structural magnetic resonance imaging (T1-weighted imaging and diffusion tensor imaging) as well as functional, i.e. blood oxygen level-dependent sensitive magnetic resonance imaging using a 3 T magnetic resonance scanner. The functional magnetic resonance imaging will be performed simultaneously to three different bladder stimulation paradigms using an automated magnetic resonance compatible and synchronised pump system.

All subjects will undergo two consecutive and identical magnetic resonance imaging measurements. Healthy subjects will not undergo any intervention between measurements but spinal cord injury patients will receive intradetrusor onabotulinumtoxinA injections for treating neurogenic detrusor overactivity.

Parameters of the clinical assessment including bladder diary, urinalysis, medical history, neuro-urological examination, urodynamic investigation as well as standardised questionnaires regarding lower urinary tract function and quality of life will serve as co-variates in the magnetic resonance imaging analysis.

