For a test-retest validation, we will additionally investigate the reliability [21] of BOLD signals in task-related fMRI in healthy controls by the intra-class correlation coefficient (ICC) for absolute or consistent agreement of participants activations over two visits.

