#### Secondary

(A) Reliability of BOLD signal changes between first and second MRI measurement in healthy controls.

(B) Correlations between clinical co-variates that are bladder diary parameters, urodynamic parameters, level of desire to void during fMRI and task-related BOLD signal intensity in supraspinal ROIs as well as structural parameters, that is, grey matter volume and number of white matter tracts between ROIs.

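### Primary outcome D is a before/after change in patients only and is read as a treatment effect, although untreated controls rescanned on the same schedule could supply a session-effect comparison

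*Protocol article*

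**What the plan says.** - **Outcome D** (Study outcome measures, Primary): "Changes of task-related BOLD signal intensity, SC and FC between ROIs in SCI patients with neurogenic detrusor overactivity before and after" the study-independent injections. No control group is named.
- **Outcomes A and B** (same list) are stated "in SCI patients with neurogenic detrusor overactivity compared to healthy controls". C names both groups.
- **Scanning schedule** (Abstract, Methods/Design): "All subjects will undergo two consecutive and identical magnetic resonance imaging measurements", and "Healthy subjects will not undergo any intervention between measurements". Under Interventions: "Two MRI measurements will be performed in identically manner within a 5 to 7 weeks interval", with no distinction by group.
- **Use of the controls' second scan** (Secondary A): "Reliability of BOLD signal changes between first and second MRI measurement in healthy controls". The end of the Background adds that this is assessed "by the intra-class correlation coefficient (ICC) for absolute or consistent agreement of participants activations over two visits". No other use is stated.
- **Interpretation** (Discussion): the study is said to show whether the injections bring about structural or functional reorganisation in the areas that control the lower urinary tract. The Abstract promises insight into the mechanism of action.

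**The concern.** A change between two scans in treated patients mixes the effect of treatment with everything else that differs between a first and a second session. Each session here is demanding: three functional paradigms of eight blocks, with repeated filling, emptying and rating. Plausible non-treatment sources of change that both groups could share are habituation to the catheter, the filling and the scanner, practice with the rating task, and scanner drift.

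Outcome D as worded has nothing to set against these sources, while the Discussion interprets it causally. A consistent second-session shift could be published as a central effect of onabotulinumtoxinA. Untreated people are being rescanned on the same schedule, so part of this ambiguity can be removed with data already planned.

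**Working it through.** **Is there a figure to reproduce?** No. The article gives no significance level, power, effect size, SD or session effect. What follows is an illustration under stated assumptions.

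**Step 1: does any stated analysis compare the two changes?** A and B are contrasts with controls, C covers both groups, D covers patients only, and secondary A covers controls only. Data analysis names the imaging software but no model. No section compares the patients' change with the controls' change.

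**Step 2: does the reliability analysis fill the gap?** For two visits, with mean squares for subjects (MSR), visits (MSC) and error (MSE):
- Consistency ICC = (MSR − MSE) / (MSR + MSE). MSC does not appear, so a uniform shift between visits leaves it unchanged.
- Absolute-agreement ICC = (MSR − MSE) / (MSR + MSE + 2(MSC − MSE)/n). A shift lowers it.

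The article leaves the choice of form open. Either form describes the controls only, is limited to BOLD, and subtracts nothing from the patients' change.

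**Step 3: what would a shared shift do to a patients-only test?** Inputs from the article: 20–24 patients (Study population and recruitment). Assumed: one region, two-sided 5% paired t-test, no treatment effect, shift s in SD units of the within-subject change. The test statistic is noncentral t with n − 1 degrees of freedom and noncentrality s√n. For s = 0.5, n = 20: noncentrality 0.5 × √20 = 2.24, critical value 2.093, rejection rate 0.565 (0.5645 before rounding).

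| Assumed shift s | n = 20 | n = 24 |
|---|---|---|
| 0 | 5% | 5% |
| 0.2 | 14% | 16% |
| 0.3 | 25% | 29% |
| 0.5 | 56% | 65% |

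**Step 4: what does a group-by-visit contrast do, and what does it cost?** The contrast is the mean change in patients minus the mean change in controls. A shift common to both groups cancels, so under the same assumptions the rejection rate stays at 5%. With equal change variance σ² in both groups, the paired standard error is σ/√n_SCI and that of the contrast is σ√(1/n_SCI + 1/n_HC). The ratio is √(1 + n_SCI/n_HC). The last column is the power of a two-sample t-test on change scores for a true effect of 0.8 SD of the change.

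| Patients / controls | Standard error ratio | Power of contrast at 0.8 SD |
|---|---|---|
| 20 / 24 | √1.833 = 1.35 | 73% |
| 24 / 24 | √2 = 1.41 | 77% |
| 20 / 12 | √2.667 = 1.63 | 56% |
| 24 / 12 | √3 = 1.73 | 59% |

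The paired test without any shift has 92% (n = 20) to 96% (n = 24) power for the same effect. The loss is real and greatest with 12 controls.

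**The case against.** **The model belongs in an unseen document.** A condensed article need not give the imaging model, and it does not say that D will be analysed by a paired test. The outcome list is also not uniform, since C names both groups without stating a comparison. This stands as far as the model is concerned: one cannot say that the investigators will not use the controls' second scan for D. But the point rests on the outcome as stated, restricted to patients, together with the causal reading in the Discussion.

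**Test-retest reliability is examined.** This is true, and an absolute-agreement ICC could reveal a shift. It would be wrong to infer that the plan ignores repeat-session variation. The safeguard is partial, for the reasons in step 2 of the working.

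**Healthy controls are an imperfect comparator.** This stands in full. A reader might infer that the planned scans suffice to isolate the treatment effect. The documents do not support that. Patients are selected as refractory and scheduled for injection, controls for having no symptoms, so regression to the mean and natural course in patients are not removed. The contrast also assumes equal session effects in both groups, which nothing in the article establishes. In the second paradigm the starting volume depends on each participant's persistent desire to void, so the stimulus itself may differ by group and visit.

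**The injections are study-independent and their effects are to be explored.** No confirmatory test or treatment decision is tied to D. This limits the severity, although the Discussion's causal wording goes beyond exploration.

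**Conclusion.** The point holds in a limited form. As stated, D cannot separate a treatment effect from a session effect common to both groups, and the only stated use of the controls' rescans does not repair this.

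The size is unknown. The range from 5% to 56–65% depends on an assumed shift of 0 to 0.5 SD, one region, an unadjusted 5% paired test and no treatment effect. A reader might take the upper figures as this study's false-positive rate. The article offers no basis for any particular shift, and with none the rate is 5%. Nor does it follow that the within-patient change should be dropped or that the contrast should be the sole primary test, given the power lost with 12 controls. The severity is should-fix.

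**What to change.** 1. For D, report the group-by-visit contrast (change in SCI patients minus change in controls) for BOLD, SC and FC, alongside the within-patient change.
2. Make any attribution to treatment depend on that contrast.
3. State that it removes only session effects common to both groups, and not regression to the mean, natural course, effects of the injection procedure or drift specific to SCI.
4. Reword the Discussion so that a within-patient change alone is not presented as something the injections caused.

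**Cost:** no additional scans are needed at the planned numbers, only wording and one further analysis. The price is precision: under equal change variances, a standard error 1.35 times (20 patients, 24 controls) to 1.73 times (24 patients, 12 controls) that of the paired test. Recruiting towards the upper end of the 12–24 control range would limit the loss.

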#### Secondary

(A) Reliability of BOLD signal changes between first and second MRI measurement in healthy controls.

(B) Correlations between clinical co-variates that are bladder diary parameters, urodynamic parameters, level of desire to void during fMRI and task-related BOLD signal intensity in supraspinal ROIs as well as structural parameters, that is, grey matter volume and number of white matter tracts between ROIs.

### Data analysis

Clinical data, for example, questionnaires scores, urodynamic parameters and 3-day bladder diary outcomes will be statistically analysed and compared between groups using IBM’s Statistical Package for the Social Sciences (SPSS) version 19.0 or newer (Armonk, New York, U.S.). The statistical analysis will be presented with means and standard deviations or with medians and interquartile ranges as appropriate.

For the analysis of the neuroimaging data, we will use statistical parametric mapping (SPM) V.8 or newer (Wellcome Department of Imaging Neuroscience, University College London, UK) and toolboxes as appropriate.

### Regulatory issues

#### Ethical approval

This study has been approved by the local ethics committee (Kantonale Ethikkommission Zürich, KEK-ZH-Nr. 2011–0346) and will be performed in accordance to the World Medical Association Declaration of Helsinki [24], the guidelines for Good Clinical Practice (GCP) [25], and the guidelines of the Swiss Academy of Medical Sciences [26]. Handling of all personal data will strictly comply with the federal law of data protection in Switzerland [27].

#### Safety

According to the safety regulations of the MR-Centre of the University Hospital Zürich, the staff involved in this study will be instructed and trained. Prior to entering the scanner room, all participants will be asked to remove any ferromagnetic items (for example, bra, chains, earrings, rings, and piercings). All participants will be provided with standardised clinical scrubs to prevent incidental import of ferromagnetic items into the MR room. To exclude UTI or pregnancy, urinalysis will be performed on every participant before urodynamic investigations and MR measurements. In case of pregnancy, the participant will be excluded from the study and referred to a gynaecologist. In case of UTI, the participant will not undergo the experiment but will be treated appropriately. After successful treatment, a reassignment to the study is possible.

In case of an adverse event (AE) or a severe adverse event (SAE), as defined by the International Organization for Standardization (ISO, 14155) [28] and the International Conference on Harmonisation (ICH) GCP guidelines (E6) [25], responsible authorities, that is, the principle investigator and the ethics committee will be informed. Appropriate actions will be executed. All AEs and SAEs will be followed as long as medically indicated.

## Discussion

This study will investigate structural and functional abnormalities and specific alterations in the brain networks of supraspinal LUT control in SCI patients with neurogenic detrusor overactivity compared to healthy controls using a multimodal imaging protocol. Importantly, effects on the supraspinal LUT control after treatment for neurogenic detrusor overactivity with intradetrusor onabotulinumtoxinA injections in SCI patients will be explored.

The findings will help to verify, amend, or adjust neuronal circuitry models established from findings in healthy controls, now in the context of SCI patients with neurogenic detrusor overactivity. Furthermore it will show whether neurogenic detrusor overactivity specific treatment such as intradetrusor onabotulinumtoxinA injections induce structural or functional reorganisation in supraspinal areas related to LUT control and in how far such changes correlate with improvements of clinical outcome parameters. These investigations will help us to understand how onabotulinumtoxinA modulates afferent pathways.

Advanced neuroimaging and evaluation techniques have the potential to serve as quantifiable outcome measures for therapy success and for improving our treatment strategies in this patient population.

### Trial status

The trial is in the recruiting phase at the time of manuscript submission.

## Abbreviations

AE: Adverse event; BOLD: Blood oxygen level-dependent; DTI: Diffusion tensor imaging; FA: Fractional anisotropy; FC: Functional connectivity; fMRI: Functional magnetic resonance imaging; GLM: General linear model; GCP: Good clinical practice; ICC: Intra-class correlation coefficient; ICH: International conference on harmonisation; ISO: International organization for standardization; LUT: Lower urinary tract; LUTS: Lower urinary tract symptoms; MR: Magnetic resonance; MRI: Magnetic resonance imaging; MD: Mean diffusivity; MNI: Montreal neurologic institute; NLUTD: Neurogenic lower urinary tract dysfunction; PVR: Post void residual; QoL: Quality of life; ROI: Regions of interest; SAE: Severe adverse event; SPM: Statistical parametric mapping; SC: Structural connectivity; SCI: Spinal cord injury; TBM: Tensor-based morphometry; UTI: Urinary tract infection; VBM: Voxel-based morphometry.
